### Role of participating centers

2.15

Our study group includes 8 centers (Turin, Modena, Genoa, Padua, Novara, and 3 centers in Milan) that have a longstanding history on ALS management, and are referral centers for ALS care following >150 patients/y each. They share an established collaboration in the field of ALS, in clinical management of patients, in the realization of clinical trials, genetic, and epidemiological studies. The analysis of biomarkers will be centralized and performed in a renowned laboratory (University of Modena and Reggio Emilia), with large experience in cell analysis and is internationally renowned for the use of flow cytometry for studies on several human diseases. Randomization and statistics will be also centralized to orchestrate the different phases of the project. Statistical Unit of the University of Modena and Reggio Emilia has considerable experience on RCT project and management, and on data analysis. All trial activities will be monitored by a CRO.

Each center is expected

1.to randomize ≥7 patients fulfilling including and excluding criteria in a period of 12 months and to administer the treatment for 18 weeks;2.to provide 1 principal investigator and 1 neurologist to evaluate including and excluding criteria, get an informed consent, administer treatment, and assess primary and secondary outcome;3.to provide a person who will send Rapamycin dosage to the coordinating center and who will not see patients; and4.to formally adhere to the practice parameters of the European Federation of Neurological Societies concerning the standardization of the management of the patient in terms of ventilatory support and nutrition.

### Ethics and dissemination

2.16

The study will be carried out in accordance with the Declaration of Helsinki, as amended by the 64th WMA General Assembly, Fortaleza, Brazil, October 2013.

The results of the study will be presented during scientific symposia or published in scientific journals only after review and written approval by the involved parties in full respect of the privacy of the participating subjects.

An insurance company will provide insurance coverage for damages emerging from the trial and involving test subjects treated with the test compound.

## Discussion

3

An urgent unmet need persists for effective therapies in ALS. The absence of reliable biomarker for disease progression and drugs activity is an important target to be addressed too. This is going to be a randomized clinical trial using a drug (Rapamycin) which potentially targets important mechanisms at play in ALS, in particular autophagy and neuroinflammation.

Preliminary data show that in 2 cell lines, inhibition of mTOR by Rapamycin reduced TDP43 fragments accumulation and restored TDP-43 nuclear localization.^[11]^ In murine and in human stem cell-derived neurons and astrocytes with mutant TDP43, autophagy enhancement improved TDP43 clearance and localization and enhanced survival, showing that autophagy induction mitigates neurodegeneration by TDP43 clearance.^[9]^ In cultured neuronal cells expressing mutant ALS-causing FUS, Rapamycin reduced FUS-positive stress granules, as well as neurite fragmentation and cell death in neurons expressing mutant FUS under oxidative stress.^[12]^ In induced pluripotent stem cells derived from ALS patient, activation of autophagic mechanisms with Rapamycin reduced the accumulation of p62.^[13]^

Early Rapamycin administration to a mouse model with FTLD and cytoplasmic TDP43 ubiquinate inclusions (UBIs) rescued learning/memory deficiencies and motor function disorders. This was associated with reduction of neuronal loss and of TDP43 UBIs.^[14]^ Treatment of zebrafish embryos with Rapamycin yielded an amelioration of locomotor phenotype in a SQSTM1 knock-down model.^[15]^

Treatment with Rapamycin of larvae of a *Drosophila* model carrying VAPB (P58S) mutation determined reversal of VAP (P58S) bouton phenotypes, and Rapamycin decreased the severity locomotive defects in a TDP-43/ALS *Drosophila* model.^[16,17]^

Furthermore, inducing autophagy with Rapamycin was shown to improve in vivo pathology of transgenic mice harboring a disease-causing VCP mutation.^[18]^

However, the failure of Rapamycin with aggravation of neuronal death has also been reported in mSOD1 mice. In this study, mSOD1 mice (which reflects the pathogenic mechanisms of SOD1 ALS, whereas the majority of ALS presents TDP43 UBIs) were treated with 2 mg/kg body weight/d, a dosage >50 times higher than that used in clinical practice (usually 2 mg/d), which gives blood concentrations that have well known toxic effects. A further study showed that this effect was due to excessive immunosuppression, as the treatment on ALS mice lacking mature lymphocytes increased ALS survival.^[23]^ However, being the evidences on Rapamycin action mainly on models linked to TDP43 pathology, we will exclude patients carrying SOD1 mutations.

As mTOR has a role in organisms longevity,^[7]^ Rapamycin has been tested to this extent and it resulted to extend the lifespan of various mouse strains.^[24]^ Rapamycin, then, has been shown to protect against several types of neuronal injury (stroke, atherosclerosis, traumatic brain, and spine injury). Recently, it resulted effective in improving respiratory function in lymphangioleiomyomatosis.^[25]^

Rapamycin has a well-known immunosuppressive action: it is used for the cure of transplanted patients, and in clinical trials to test efficacy in autoimmune disorders, CNS tumors, and other neurological disorders (such as tuberous sclerosis).

As for the role of immunity in ALS, recent studies suggest that innate and adaptive immune systems contribute to ALS progression: Msod1 Tregs cocultured with activated Msod1 microglia attenuated the expression of microglial toxic factors by IL4 release, and promoted MN survival by suppressing M1 activation, inducing an M2 protective phenotype, and reducing the release of ROS. Tregs passive transfer into ALS mice prolonged survival, and FoxP3 mRNA in mSOD1 mice spinal cord decreased with disease progression.^[8]^ In patients, blood Treg percentage inversely correlated with ALS progression rate, and FoxP3 levels were early predictors of ALS progression and survival. These data were confirmed in postmortem studies.^[8]^ Inhibiting the mTOR pathway, Rapamycin induces de novo FoxP3 expression and expands Treg.

The entity of the increase of Tregs induced by Rapamycin is completely unknown in ALS patients. For this reason, we are planning this first trial focused on showing immunological targets engagement by Rapamycin in ALS patients. Moreover, given its large natural structure, there was initial concern that Rapamycin might not be able to cross the BBB; however, in one study sufficient levels of Rapamycin could be found in brain tumors when administered at therapeutic doses.^[26]^ To further address this concern, we are planning to test Rapamycin titer in CSF at treatment end with LC–MS/MS (using HPLC). This procedure will also allow to understand if Rapamycin action depends on BBB crossing or on its action on Treg cells.

In conclusion, the study will give extensive inference to a possible effect of Rapamycin on biomarkers of disease progression. Rapamycin is an already approved drug, with known pharmacokinetics, which is available and therefore there is significant possibility of transferability to patients, and of a rapid translation to daily clinics.

This short study will optimize time and resources to get reliable information for a following RCT to test Rapamycin clinical efficacy in ALS.

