**Methods::**

RAP-ALS is a phase II randomized, double-blind, placebo-controlled, multicenter (8 ALS centers in Italy), clinical trial. The primary aim is to assess whether Rapamycin administration increases Tregs number in treated patients compared with control arm. Secondary aims include the assessment of safety and tolerability of Rapamycin in patients with ALS; the minimum dosage to have Rapamycin in cerebrospinal fluid; changes in immunological (activation and homing of T, B, NK cell subpopulations) and inflammatory markers, and on mTOR downstream pathway (S6RP phosphorylation); clinical activity (ALS Functional Rating Scale-Revised, survival, forced vital capacity); and quality of life (ALSAQ40 scale).

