### Objectives

2.1

The primary objective is to assess whether different Rapamycin doses increase Treg number in ALS patients compared with the control arm.

Secondary objectives include the following:

1.*Assessment of Rapamycin safety and tolerability in a cohort of ALS patients*: occurrence of adverse events (AEs), changes on clinical examination including vital signs and weight, and laboratory examinations (biochemistry, hematology and urinalysis) will be registered throughout the entire study duration.2.*Biological assessment*: To analyze Rapamycin efficacy in inhibiting MTOR pathway, by quantifying the phosphorylation of the S6 ribosomal protein (S6RP) comparing baseline and weeks 8, 18 (treatment end), 30, and 54 between Rapamycin arms and placebo arm. To identify changes in activation and homing capabilities of different T, B, NK cell subpopulations comparing baseline and weeks 8, 18 (treatment end), 30, and 54 between Rapamycin arms and placebo arm. To study Rapamycin effects on different biomarkers (including peripheral and CSF biomarkers, that is, creatinine and albumin, CK, vitamin D, plasma/CSF neurofilament heavy/light chain protein) comparing baseline and week 8, 18 (treatment end), 30, and 54 between Rapamycin arms and placebo arm. To identify Rapamycin-induced changes in inflammatory status, by the molecular analysis of the inflammasome system baseline and week 8, 18 (treatment end), 30, and 54 between Rapamycin arms and placebo arm. To assess Rapamycin capacity to pass through blood–brain barrier (BBB).3.*Clinical assessment*: to assess changes in Amyotrophic Lateral Sclerosis Functional Rating Scale (ALSFRS)-Revised from baseline to weeks 4, 8, 12, 18, 30, 42, and 54 in placebo and treatment arms; overall survival from randomization to date of documented death or tracheostomy; survival rate at weeks 18, 30, 42, and 54; forced vital capacity (FVC) score from baseline to weeks 4, 8, 12, 18, 30, 42, and 54.4.Quality of life assessment: ALSAQ-40 from baseline to weeks 8, 18, 30, and 54 in treatment and placebo arms.

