### Treatment and blindness

2.7

This study is a phase II randomized, double-blind, placebo-controlled, multicenter, clinical trial (RCT) to test Rapamycin in ALS patients. The study will include 63 ALS patients (EL Escorial Revised Criteria, sporadic and familial) with 1:1:1 allocation in 3 groups of 21 subjects each; treatment will be double blinded, and will last 18 weeks. Active treatment will include oral Rapamycin at 1 mg/m^2^/d or 2 mg/m^2^/d.

Rapamycin levels will be regularly measured and revealed only to an independent monitor, who will input Rapamycin levels on a separate eCRF, and on the basis of that value dosing changes may be performed at each treatment dispensation directly through eCRF (and blinded to caring neurologists who will supply bottles identified by a number and corresponding to different blinded doses) to keep Rapamycin levels from 4 to 12 ng/mL. Computerized randomization will be stratified by ΔFS (</≥0.7).

After treatment end (week 18) patients will be followed up for further 36 weeks. This large period of follow-up has the aim to assess potential late side effects of the treatment and to assess whether eventual biological or clinical effects of the treatment with respect to placebo, may last after drug discontinuation.

For the first 10 patients enrolled, clinical and biological safety assessments will be performed every week for the first month, and then every 2 weeks until the end of treatment. For the remaining 53 patients clinical assessments will be performed every 2 weeks for the first month, and then every 4 weeks during treatment duration.

If at either the interim or the final analyses safety concerns will arise, the trial will be stopped and all available data will be reviewed by the Study Steering Committee.

Table 2 shows study procedures to be undertaken.

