### Outcomes

2.9

The primary outcome is represented by the change from baseline to week 18 in Treg number in ALS patients treated with Rapamycin compared with the control arm.

Secondary outcomes are as follows:

1.*Safety*: Occurrence of AEs and per-treatment arising changes in physical examination, vital signs (blood pressure, pulse rate, and body temperature), body weight, and clinical laboratory tests (biochemistry, hematology). MedDRA dictionary is going to be used for reporting.2.*Rapamycin levels in CSF* at week 18 (high-performance liquid chromatography (HPLC) with mass spectrometry (MS) (LC–MS/MS).3.Change from baseline to each time point (weeks 8, 18, 30, and 54) of the phosphorylation of the S6 ribosomal protein *(S6RP)* comparing Rapamycin arms and placebo arm.4.Change from baseline to each time point (week 8, 18, 30, and 54) of the activation and homing capabilities of different *T, B, NK cell subpopulations* comparing Rapamycin arms and placebo arm.5.Changes from baseline to each time point (weeks 8, 18, 30, and 54) in different *biomarkers* (including peripheral and CSF biomarkers that is, creatinine and albumin, CK, vitamin D, plasma/CSF neurofilament heavy/light chain protein) comparing Rapamycin arms and placebo arm.6.Changes from baseline to each time point (weeks 8, 18, 30, and 54) in *inflammatory status (molecular analysis of the inflammasome system)* comparing Rapamycin arms and placebo arm.7.Change from baseline to each time point (weeks 4, 8, 12, 18, 30, 42, and 54) of *ALSFRS-R.*8.*Survival* defined as the time from randomization to the date of documented death or tracheotomy.9.Survival rate at weeks 18, 36, and 54.10.*Change of FVC* from baseline to each time point (weeks 4, 8, 12, 18, 30, 42, and 54).11.Absolute and relative change from baseline in *ALSAQ-40* (Amyotrophic Lateral Sclerosis Specific Assessment Questionnaire at weeks 4, 8, 12, 18, 30, 42, and 54).

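### The week-18 CSF titre can show whether Rapamycin reaches the CSF, but not, as the Discussion says, whether it acts by crossing the BBB or through Tregs

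*Protocol article*

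**What the plan says.** The Discussion (section 3) raises the worry that the molecule may not cross the blood–brain barrier and answers it with a measurement: "we are planning to test Rapamycin titer in CSF at treatment end with LC–MS/MS (using HPLC". The next sentence attaches a second purpose: "This procedure will also allow to understand if Rapamycin action depends on BBB crossing or on its action on Treg cells". It carries no qualification.

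The operative sections are narrower:

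- Objectives (2.1) asks only whether the drug gets across the barrier.
- Outcomes (2.9) lists, as the second secondary outcome, "Rapamycin levels in CSF* at week 18". That is the only CSF drug measurement named.
- The Methods part of the abstract puts the same aim in terms of dose: "the minimum dosage to have Rapamycin in cerebrospinal fluid".

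On Tregs, Objectives says: "The primary objective is to assess whether different Rapamycin doses increase Treg number in ALS patients compared with the control arm". The Discussion gives the mechanism: "Inhibiting the mTOR pathway, Rapamycin induces de novo FoxP3 expression and expands Treg".

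On blood levels, Treatment and blindness (2.7) says: "Rapamycin levels will be regularly measured and revealed only to an independent monitor". Dose may then be changed to hold the level between 4 and 12 ng/mL.

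**The concern.** Separating two routes of action requires patients in whom one route is open and the other closed, or an analysis that can credibly stand in for that contrast. Here the drug is oral in both active arms, so anyone with drug in the CSF also has drug in the blood acting on Tregs. The article itself treats dose as the source of both CSF presence and Treg increase. CSF level and Treg response therefore share a cause, and neither CSF level nor achieved blood level is randomised.

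The trial is meant to inform a later efficacy trial. If drug in CSF together with a biological or clinical effect were read as central action, that reading could shape the next trial's biomarkers and endpoints without support. Conversely, a low CSF level in a patient who had stopped or interrupted drug before week 18 could be misread as failure to cross the barrier.

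**Working it through.** **Step 1. What each possible result would say about route**

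| CSF drug at week 18 | Effect seen | Still on drug | What it says |
|---|---|---|---|
| Detected | Yes | Yes | Fits central action, Treg action, or both |
| Detected | No | Yes | The drug crosses; nothing about the route of an effect that is absent |
| Not detected | Yes | Yes | Argues against direct CNS action |
| Not detected | Either | No | Says nothing about crossing, since there was no current exposure |

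Only the third row bears on route, and in one direction. The two dose arms do not add a contrast: both expose blood, and dose changes toward one common blood range make achieved exposure a post-randomisation quantity. The Adverse events section (2.10) provides for interruption and discontinuation, so the fourth row can occur.

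**Step 2. Number of patients for the illustration**

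Section 2.13 gives 54 evaluable patients in three arms. The usual two-proportion formula (50% versus 5%, two-sided alpha 0.025, power 0.80, no continuity correction) gives 18 per arm, and 3 × 18 = 54, so the stated figure reproduces. Active patients: 2 × 18 = 36. That all 36 provide CSF is an assumption.

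**Step 3. CSF–effect correlation with no CNS action**

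Suppose blood level drives CSF level and also drives the effect, and CSF level does nothing. Then

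r(CSF, effect) = r(blood, CSF) × r(blood, effect).

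The documents give neither correlation, so both are assumptions shown over a range. Worked example: 0.7 × 0.5 = 0.35. Fisher's z is 0.365, and 0.365 × √(36 − 3) = 2.10, just above 1.96, so slightly more than half of such trials would be nominally significant at two-sided 5%. Simulation with 5,000 runs per row:

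| Blood–CSF | Blood–effect | Expected CSF–effect r | Nominally significant |
|---|---|---|---|
| 0.5 | 0.3 | 0.15 | 14% |
| 0.5 | 0.5 | 0.25 | 31% |
| 0.7 | 0.3 | 0.21 | 23% |
| 0.7 | 0.5 | 0.35 | 55% |
| 0.9 | 0.3 | 0.27 | 37% |
| 0.9 | 0.5 | 0.45 | 82% |

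**Step 4. Does adjustment for blood level repair it?**

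With blood level measured without error, the numerator of the partial correlation is r(CSF, effect) − r(blood, CSF) × r(blood, effect) = 0, and the simulated rate returns to 4.5% to 5.3%.

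With error it does not. A second simulation (20,000 runs, 36 patients) used the chain blood → Treg → outcome plus blood → CSF, with all three path correlations equal and an assumed blood-level reliability of 0.6:

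| Each path | Expected r = path³ | Unadjusted | Adjusted, no error | Adjusted, reliability 0.6 |
|---|---|---|---|---|
| 0.5 | 0.13 | 11% | 5.1% | 6.4% |
| 0.7 | 0.34 | 55% | 5.1% | 17.4% |
| 0.8 | 0.51 | 91% | 5.2% | 42.5% |
| 0.9 | 0.73 | 100% | 5.2% | 91.4% |

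So adjustment helps, but cannot be relied on to turn the association into evidence of mechanism.

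**The case against.** The strongest reply is that the fault is one Discussion sentence, not the trial. The objective asks only about crossing, the outcome is only a drug level, and Statistical analyses (2.14) describes between-arm comparisons with no correlation of CSF level with anything. The titre also has some value for the route question: an effect without CSF drug would point away from direct CNS action, and no correlation is needed to say so. All of this stands, and it sets the limits of the point.

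The figures above are likewise open to challenge. They belong to a test that the article does not plan, and they rest on assumed correlations. Holding blood levels at 4–12 ng/mL narrows exposure and may weaken the spurious link. They illustrate a risk and do not estimate an error rate of this trial.

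A reader might go further and infer that the trial has a planned mechanism analysis with a false-positive rate of up to 82%, or that the missing mediation analysis is itself a defect. The documents support neither. No such test is stated, and any exploratory analysis could sit in the full protocol or analysis plan, which are not shown.

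What the reply does not remove is the sentence itself. It promises an either/or answer. The routes are not mutually exclusive, and detected drug with an effect cannot tell them apart.

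**Conclusion.** The point holds as a specific overclaim about what the trial can conclude. The week-18 titre can answer whether the drug is present in CSF, and one result pattern would argue against direct CNS action. It cannot establish central action or attribute an effect to one route.

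The argument in Step 1 needs no assumed figure. It rests on oral dosing in both active arms, on the article's own treatment of dose as driving both CSF presence and Tregs, and on the single CSF drug measurement. The 14% to 82% range applies only if the inference were drawn from an unadjusted CSF–effect association in 36 patients under the stated correlations.

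It would be wrong to infer that the CSF outcome is uninformative or that the primary result is at risk. The Treg comparison between arms is randomised and does not use CSF level, and neither the sample size nor the safety rules depend on it.

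**What to change.** - Replace the Discussion sentence with one limited to CSF penetration, in line with the objective in section 2.1. That objective and the CSF outcome in section 2.9 need no rewording.
- Report each CSF level with a blood level from the same day, taken from the monitoring already planned, and give the CSF-to-blood ratio. Interpret barrier passage only in patients still on drug at the lumbar puncture.
- If a CSF–outcome association is examined, label it exploratory, adjust it for blood level, state that the adjustment is incomplete when blood exposure is measured with error, and draw no claim of mechanism from it.

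The cost is a changed sentence and making sure that one planned blood level coincides with the CSF sample. No arm, patient or dosing rule changes. The sponsor gives up a mechanism claim that the design could not support.
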